## Methods/design

### Trial design

The study is a single-center, prospective, randomized controlled trial (RCT) with two measurement time points. Relatives of lung cancer patients and, thus, the patients themselves (i.e., dyads) are randomly assigned to the CALM intervention group (IG) or the control group (CG) regardless of their disease or treatment stage. The relatives in the IG will receive psycho-oncological support according to the CALM manual, whereas the relatives in the CG will receive usual psycho-oncological treatment (usual care). However, the patients in both study arms will not get a specific intervention. The relatives and the patients complete the assessments at baseline (T0) and after the intervention (IG, T1) or after 6 weeks (CG, T1). Figure 1 shows the study workflow, and Table 1 shows the SPIRIT reporting guideline schedule.

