**Methods:**

The study is a single-center, prospective, randomized controlled trial with two measurement time points. Relatives of lung cancer patients and, thus, the patients themselves (i.e., dyads) are randomly allocated to the intervention group (IG) or the control group (CG) regardless of their disease or treatment stage. Relatives in the IG receive structured counseling based on the CALM approach (three to six sessions with psycho-oncologists). The CG receives usual psycho-oncological care. In addition, cancer patients in both study arms can request psycho-oncological support (usual care) as needed, but they will not get a specific intervention. Relatives and patients complete assessments at baseline (T0) and after the intervention/6 weeks (T1). The primary outcome for relatives is anxiety. Relatives’ secondary outcomes include depressive symptoms, distress, supportive care needs, and quality of life. Patients’ outcomes include anxiety, depression, and distress. All outcomes are assessed using self-report validated questionnaires. Intervention effects will be evaluated using analysis of covariance (ANCOVA) adjusting for baseline values. Power calculations reveal the need to enroll 200 subjects to detect an effect of *d* = 0.4.

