### Intervention

#### Intervention group (IG)

The intervention condition is a structured psycho-oncological intervention based on the Managing Cancer And Living Meaningfully (CALM) manual. CALM is an individualized, evidence-based psychotherapeutic intervention that focuses on four domains relevant to the challenges typically experienced by cancer patients:Symptom management and communication with healthcare providersChanges in self and relations with close othersSpiritual well-being and a sense of purposeConcerns related to the future and mortality [28]

The topics covered in the CALM domains are also relevant for relatives. Adaptations of the intervention therefore refer to the fact that in all domains, the well-being (e.g., physical and psychological symptoms) and the self-perception of the relative (e.g., change in values since the relative’s illness) are explored instead of the well-being and perception of the patient.

The CALM domains should be addressed in a tailored, individualized manner that allows for variation in time spent on each domain and the number of sessions based on the participants’ needs. Therefore, each relative receives three to six counseling sessions, each lasting 45 min. A CALM-trained psychologist delivers the sessions within 6 weeks. Three psychologists of the CCCMF (experienced psycho-oncologists/psychotherapists) were trained to do the CALM intervention at the psycho-oncological department.

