**Further variables**						
Sociodemographic data	Gender, age, education level, relationship to family member/patient, previous psychological treatment	5	X	–	X	–
Medical data	Date of diagnosis, histological subtype, UICC tumor stage, smoking	4	–	–	X	–
Treatment integrity	Number of counseling sessions	1	–	X	–	X

*T0* baseline, *T1* after intervention/6 weeks, *UICC* Union for International Cancer Control

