### Recruitment

Lung cancer patients treated in the University Hospital Würzburg and their relatives are recruited either in the pneumatological outpatient clinic or by contacting the patients or their relatives by phone. Eligible persons are informed about all relevant aspects of the study, i.e., the psycho-oncological intervention for the relatives, the procedure, and assessments. It is also explained that participation in the study is voluntary and can be terminated at any time without giving a reason. In the case the patients and their relatives are interested in the study, they get written study information, a flyer with the offers of the psycho-oncological department of the CCCMF, the baseline set of questionnaires (T0), and an informed consent form (in person or delivered by mail). After written consent is provided and the initial questionnaires (T0) are completed, a psycho-oncologist will contact relatives in the IG to set a date for an initial appointment, whereas CG will not be actively contacted.

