## Discussion

Psycho-oncological care usually focuses on the patients themselves. However, relatives of lung cancer patients often suffer from distress that might affect their mental health and quality of life. Psychosocial interventions can alleviate this burden. However, structured interventions for relatives are not usual care so far. Furthermore, further research on interventions for different types of cancer and well-powered trials are warranted. In this RCT, we evaluate the short-term effectiveness of a CALM intervention compared to usual psycho-oncological care for relatives of lung cancer patients. In addition, the effects on the patients will be explored. The study aims to evaluate individual CALM counseling for relatives. Individual counseling is different from couple/family counseling, and we therefore decided on a clear delineation.

Methodological challenges might arise from the delineation of study conditions. For example, based on ethical concerns, it is also possible for the relatives in the CG to receive psycho-oncological support at the CCCMF or other psychosocial cancer counseling centers (usual care). On the other hand, counseling in the IG varies between 3 and 6 sessions, and relatives can decline conversations at any time. Consequently, it is also interesting to compare relatives who had no or few conversations with relatives who experienced more intensive care, quantifiable, for example, by the number of meetings as an independent variable. Furthermore, the estimation of effect size is challenging due to the heterogeneous results of previous studies. On the other hand, there is a high effort in recruiting this vulnerable group and human resources to deliver the structured intervention. Therefore, we plan an interim analysis to estimate the effects considering resources and meaningfulness.

Limitations are that the study period is restricted, and only short-term effects at the end of the intervention will be evaluated. Therefore, the effects over more extended periods will remain unclear. Further studies will be warranted to examine the longer-term effectiveness of the CALM intervention for relatives.

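### T1 is set by the end of the intervention in the IG and by the calendar in the CG, so time since baseline can differ by arm on the primary outcome

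*Protocol article*

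**What the plan says.** The Trial design section states that participants "complete the assessments at baseline (T0) and after the intervention (IG, T1) or after" 6 weeks in the CG. The Methods part of the abstract and the Table 2 footnote use the same double definition, the footnote as "after intervention/6 weeks". The visible text gives no common date or window.

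The length of the IG course is flexible. Under Intervention group (IG), "each relative receives three to six counseling sessions, each lasting 45 min", and the approach "allows for variation in time spent on each domain and the number of sessions". The same section has the sessions delivered within 6 weeks, without saying whether this runs from T0, from randomisation or from the first session. Under Recruitment, once consent and T0 are complete, "a psycho-oncologist will contact relatives in the IG to set a date for an initial appointment, whereas CG will not be actively contacted". No maximum wait for that appointment is given.

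The Discussion adds that "relatives can decline conversations at any time". Under Monitoring: harms, reasons for discontinuing are documented. Under Statistical analysis, endpoints are analysed by intention to treat with ANCOVA adjusted for baseline values, and values missing through drop-out are handled by pair-wise deletion.

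**The concern.** A randomised comparison at follow-up isolates the treatment effect only if both arms are measured on the same clock. If relatives' anxiety drifts over the weeks for reasons unrelated to counselling, and one arm is measured systematically earlier or later, the drift enters the arm difference. Baseline adjustment corrects for where people started, not for how long they were followed. In the IG the interval also depends on what happens after randomisation: the wait for an appointment, the number of sessions and when they end.

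Second, a relative in the IG who declines all sessions or breaks off has no clear end of intervention. Intention to treat still needs a T1 from that person. If T1 were not sent, the loss would fall in one arm only.

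This affects the sole primary outcome at its only follow-up, the secondary and patient outcomes collected at the same T1, and the interim decision, which depends on the observed effect size.

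**Working it through.** **What T1 means in each arm**

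- CG: T1 at 6 weeks (Trial design). The origin of the 6 weeks is not stated.
- IG: interval from T0 = wait for the first appointment + duration of sessions.
- If the 6-week delivery limit runs from T0, the end of the IG course falls at or before week 6. A three-session course could end well before it.
- If the limit runs from the first session, the course can end as late as the wait plus 6 weeks, so after week 6.

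Both readings fit the text. The mean gap between arms (mean IG interval minus 6 weeks) can therefore be negative, near zero or positive.

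**The plan's own figure**

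Inputs from Sample size calculation and Statistical analysis: d = 0.4, two-sided alpha 0.05, power 0.80, equal allocation.

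- n per arm = 2 × (1.960 + 0.842)² / 0.4² = 98.1, rounded up to 99, or 198 in total. The t-test version gives 99.08, so 100 per arm. The stated 200 reproduces and is not in question.
- Standard error of the standardised difference at 100 per arm = √(2/100) = 0.141.
- Power at d = 0.4: 0.4 / 0.141 = 2.83; Φ(2.83 − 1.96) = 0.807.

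**Illustration of a timing gap**

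Bias = common drift per week × mean gap in weeks. Neither input is in the document; both are assumed here.

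| Drift (SD/week) | Gap (weeks) | Bias (SD) | Share of 0.4 | Two-sided type I error | Power at d = 0.4 if the bias runs against the IG |
|---|---|---|---|---|---|
| 0.02 | 1 | 0.02 | 5% | 0.052 | 0.766 |
| 0.05 | 2 | 0.10 | 25% | 0.109 | 0.564 |
| 0.10 | 3 | 0.30 | 75% | 0.564 | 0.105 |

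Middle row: 0.10 / 0.141 = 0.707. Type I error = [1 − Φ(1.96 − 0.707)] + Φ(−1.96 − 0.707) = 0.105 + 0.004 = 0.109. Power = Φ(0.30 / 0.141 − 1.96) = Φ(0.16) = 0.564. These figures use the unadjusted standard error.

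The last row is extreme. A mean gap of 3 weeks needs the average IG relative to be assessed at about week 3 or week 9, and 0.10 SD per week means 0.6 SD of common drift over 6 weeks.

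**Recall window**

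The GAD-7 refers to the previous two weeks. Moving T1 by one week replaces half of that window, and moving it by two weeks replaces all of it.

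**The case against.** The strongest reply is that the arms are nominally aligned: delivery within 6 weeks in the IG looks chosen to match 6 weeks in the CG, and Table 1 has a single t1 column. If the limit runs from T0 and most courses fill it, the gap is small. Early and late assessments also partly cancel in the mean. Enrolment is open at any disease or treatment stage, so time since diagnosis gives no obvious common direction of drift. All of this stands, and it limits what can be claimed about size. It does not supply a common anchor or window.

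Three stronger readings are tempting, and the document does not support them.

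- A reader might infer that the primary comparison is definitely biased, or by a given share of d = 0.4. No drift and no achieved interval is reported, so neither size nor sign follows.
- A reader might infer that relatives who improve finish early, making IG timing outcome-dependent. The plan says only that the number of sessions follows participants' needs.
- A reader might infer that IG relatives who stop are not followed up. Nothing says so. T1 is mailed rather than tied to a session, and nonresponders are telephoned (Data collection). This softens the point about non-starters, but does not say when their T1 falls due.

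Figure 1 and the full protocol are not shown and may hold more timing detail. The abstract, the design text and the table footnote nevertheless all carry the arm-dependent definition.

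Finally, the Discussion gives the aim as short-term effects when the intervention ends. A fixed T1 answers a slightly different question for relatives still in counselling, which is a real cost of the change.

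**Conclusion.** The point holds as a weakness in how T1 is defined. T1 follows an event in one arm and the calendar in the other, the two can diverge in either direction, and the stated ANCOVA does not correct for unequal elapsed time. For IG relatives who stop or never start, the IG definition gives no assessment date, which sits badly with the intention-to-treat commitment.

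The size of any bias is unknown. The 0.10 SD example rests wholly on an assumed 0.05 SD per week and a 2-week mean gap. If the delivery limit runs from T0 and is largely used, the effect may be negligible. The case for acting is that the remedy is cheap and the affected comparison is the primary one, not that bias has been shown.

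**What to change.** - Define T1 at one common time from T0 or from randomisation in both arms, such as the 6 weeks already used in the CG, with the anchor stated and one common window.
- Mail T1 to all randomised relatives and patients at that time, whatever the number of sessions attended, including those who stop or never start.
- Enrolment began on 30.09.2020, so some participants will have been assessed under the present definition. Where completion or mailing dates exist, report T0–T1 intervals by arm and add a sensitivity analysis restricted to a common window or adjusted for the interval. The document does not say that these dates are recorded, so this must be checked first.
- An end-of-intervention questionnaire in the IG can stay as an exploratory measure.

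Cost: a change to the mailing schedule and protocol wording, and an ethics amendment. The planned 200 relatives are unaffected. Some IG relatives will be assessed before their last session, which may slightly reduce the estimated effect. The definition of T1 also changes during the trial, so the report should state who was assessed under which definition.

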**Fig. 1 Fig1:**
[figure not shown]
Study protocol diagram of data collection processes

**Table 1 Tab1:** SPIRIT schedule of enrollment, interventions, and assessments

	**Study period**				
	**Enrollment**	**Baseline**	**Allocation**	**Post-allocation**	
**Time point**	*** − t***_**0**_	***t***_**0**_			***t***_**1**_
**Enrollment**					
Eligibility screen	X				
Informed consent	X				
Randomization			X		
**Interventions**					
Intervention: CALM					
Control: usual care					
**Assessments**					
**Relatives**					
GAD-7		X			X
PHQ-9		X			X
DT		X			X
SNCS		X			X
CQOLC		X			X
Sociodemographic data		X			
**Patients**					
GAD-7		X			X
PHQ-9		X			X
DT		X			X
Sociodemographic data		X			
Medical data		X			

### Study setting and participants

This study is performed at the University Hospital Würzburg, Comprehensive Cancer Center Mainfranken (CCCMF), Germany.

The eligibility criterion for participants is being a relative of a patient with lung cancer (ICD-10: C34). Relatives are defined as spouses, children, parents, other family members, and close friends or caregivers. Relatives and patients are included regardless of the stage of disease, histology, staging, and choice of therapy or treatment. Further criteria are the age of 18 years or older (of the relative and the patient) and the ability to give informed consent. The exclusion criteria are a lack of German language abilities or a pre-diagnosed mental illness of the relative.

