A tool that might be helpful in the psychological support of relatives is the Managing Cancer And Living Meaningfully (CALM) intervention. CALM is a brief, tailored, supportive-expressive psychotherapeutic intervention that intends to treat and prevent depression and end-of-life distress in patients with advanced cancer. It provides a therapeutic relationship and reflective space about four domains: symptom management and communication with health care providers, changes in self and relations with close others, spiritual well-being and the sense of meaning and purpose, and mortality and future-oriented concerns [26]. CALM is feasible and effective in patients with advanced cancer. Patient-identified unique benefits of the intervention are [1] a safe place to process the experience of advanced cancer, [2] permission to talk about death and dying, [3] assistance in managing the illness and navigating the healthcare system, [4] resolution of relational strain, and [5] an opportunity to “be seen as a whole person” within the healthcare system [27]. A controlled study showed the positive effects of CALM on depressive symptoms, coping, and psychological well-being in patients with advanced cancer [28]. However, to our knowledge, no study applied the CALM manual to support relatives. Therefore, we conducted the following study with relatives of patients with lung cancer.

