### Assignment of interventions

#### Randomization and allocation concealment

All participants, i.e., dyads of relatives and lung cancer patients, will be randomly assigned to IG or CG after consent is given and initial questionnaires (T0) are completed.

A block randomization procedure with an allocation ratio of 1:1 is used. A member of the study center (not involved in the study) created the randomization list with computer-generated random numbers linked to the research codes (i.e., a consecutive list of numbers). The research code is used on all questionnaires and medical data instead of the name (pseudonymization; see confidentiality). The list is stored locked at the study center. Research codes are printed on the first questionnaires (T0). Therefore, assignment based on the sequence of the list is determined by the time of receipt of the interest to participate and, consequently, the distribution of the study information, consent form, and questionnaire. Allocation concealment will be ensured, as the study members responsible for enrollment (i.e., study coordinator) will not release the randomization number until the signed consent form and baseline assessments have been completed.

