#### Main research question

The primary and secondary endpoints will be analyzed according to the intention-to-treat principle. Treatment effects (between-group effects) in primary and secondary outcomes will be evaluated using analysis of covariance (ANCOVA) adjusting for baseline values. Statistical significance (*p* < 0.05, two-sided) and effect sizes (*ή*^2^) will be reported for all between-group differences [27]. In addition, within-group effects, including standardized effect sizes (SES) and accompanying 95% confidence intervals (CIs), will be calculated for both study groups.

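### UICC stage is collected at T0 in an all-stage trial of an intervention developed for advanced cancer, but the stated ANCOVA does not adjust for it: a small, cheap loss of precision and pre-specification, not a validity error

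*Protocol article*

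**What the plan says.** Study setting and participants sets no limit on stage: "Relatives and patients are included regardless of the stage of disease, histology, staging, and choice of therapy or treatment". Trial design repeats this for the randomised dyads.

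Background and rationale says that CALM "intends to treat and prevent depression and end-of-life distress in patients with advanced cancer", and summarises the evidence as "CALM is feasible and effective in patients with advanced cancer". It adds that, "to our knowledge, no study applied the CALM manual to support relatives". The Intervention section explains how the content is adapted from patient to relative and tailored to individual need. It does not discuss the step from advanced to earlier disease.

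Table 2 lists the medical data taken for patients at T0: "Date of diagnosis, histological subtype, UICC tumor stage, smoking". In Statistical analysis the only stated use of medical data is descriptive. Under Main research question, treatment effects in the primary and secondary outcomes "will be evaluated using analysis of covariance (ANCOVA) adjusting for baseline values". On allocation, the article says "A block randomization procedure with an allocation ratio of 1:1 is used" and names no stratification factor.

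Blinding states that the analysts are not blinded and that team members combine enrolment, data collection and analysis. The end of the Discussion says that CALM should enter routine care if the relatives' outcomes improve, and does not mention stage.

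**The concern.** The enrolled population is wider than the setting in which CALM was developed and tested. Background and rationale itself links relatives' vulnerability to late diagnosis, rapid progression and poor prognosis. Stage is therefore a plausible predictor of how a relative's anxiety moves over 6 weeks, beyond what the T0 score captures, and a plausible modifier of the effect. The trial collects it, but the stated model does not use it.

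Three things are at stake, all modest:

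- some precision in the primary comparison;
- chance imbalance on stage, which is most likely if the trial ends at the interim of 88;
- pre-specification. If stage turns out imbalanced, analysts who know the allocation would have to decide after seeing the data whether to add it.

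A reader of a positive result would also want to know what the data say outside advanced disease, and the article describes no such estimate.

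**Working it through.** **Inputs from the article.** d = 0.4, alpha 0.05 two-sided, beta 0.2, 100 per group; interim at 44 per group, linked to d = 0.6 (Sample size calculation, Main research question).

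**Assumptions.** The article gives neither the stage mix nor the effect of stage on GAD-7. I take 50% to 80% of patients as advanced, and a stage effect of 0.1 to 0.5 SD on the score after baseline adjustment. The simulation uses blocks of 4.

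**1. The plan's own sample sizes.** n per group = 2(1.96 + 0.842)²/d².
- d = 0.4: 98.1, so 99; the t-test version gives 99.08, so 100 per group and 200 in total. This reproduces the plan.
- d = 0.6: 43.6, so 44 per group and 88 in total. This reproduces the plan under the normal formula (the t-test version gives 44.6).

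Neither figure depends on stage.

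**2. Chance imbalance.** SD of the between-arm difference in the advanced share = √(2p(1−p)/n), if stage is not used in allocation.

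| Per group | Advanced share p | SD (points) | P(gap > 10 points) | P(gap > 20 points) |
|---|---|---|---|---|
| 100 | 0.5 | 7.1 | 15.7% | 0.5% |
| 100 | 0.7 | 6.5 | 12.3% | 0.2% |
| 100 | 0.8 | 5.7 | 7.7% | 0.0% |
| 44 | 0.5 | 10.7 | 34.8% | 6.1% |
| 44 | 0.7 | 9.8 | 30.6% | 4.1% |
| 44 | 0.8 | 8.5 | 24.1% | 1.9% |

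At p = 0.5 the 95% range is 1.96 × √(0.5/100) = ±13.9 points at 100 per group and 1.96 × √(0.5/44) = ±20.9 points at 44 per group.

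**3. What imbalance does to the estimate.** Shift in d = gap × stage effect.
- A 10-point gap: 0.10 × 0.1 = 0.01 up to 0.10 × 0.5 = 0.05.
- The edge of the 95% range at p = 0.7 with a 0.5 SD effect: 0.064 at 100 per group and 0.096 at 44 per group.
- For comparison, the SE of d is √(2/100) = 0.141 and √(2/44) = 0.213.

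The interim thresholds of 0.4 and 0.6 lie 0.2 apart, so a 10-point gap moves d by at most a quarter of that distance. The SE alone already exceeds it.

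**4. Validity.** I simulated an ANCOVA with p = 0.7, a stage effect of 0.5 SD on both scores, a baseline coefficient of 0.6 and 20,000 runs. Type I error was 5.2% with stage omitted and 5.0% with it included, and the mean estimate was 0.00 both times. The Monte Carlo SE is √(0.05 × 0.95/20000) = 0.15 points.

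**5. Precision.** Stage explains p(1−p)g² of the variance, and power = Φ(0.4/√((1 − p(1−p)g²) × 2/100) − 1.96). Without stage it is 0.807. At p = 0.7:
- g = 0.2: variance 0.0084, power 0.811
- g = 0.3: variance 0.0189, power 0.815
- g = 0.5: variance 0.0525, power 0.828

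The gain is 0.4 to 2.1 points.

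**6. Effect by stage.** With n₁ and n₂ per arm in the two stage groups, SE of the interaction = √(2/n₁ + 2/n₂).
- 20% non-advanced: √(2/20 + 2/80) = 0.354; power for an interaction of 0.4 is Φ(0.4/0.354 − 1.96) = 20%.
- 50% non-advanced: √(2/50 + 2/50) = 0.283; power 29%.

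Power for d = 0.4 within the non-advanced group is 24% to 52% over the same range.

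**The case against.** The strongest reply is that this is a preference about covariates. Broad entry is deliberate, and the background reasons given for it apply to lung cancer as a whole. The content is adapted for relatives and tailored, and taking CALM to relatives is the purpose of the trial. Baseline GAD-7 already absorbs part of any stage effect. Chance imbalance is already reflected in the standard error, and the power gain is slight. Most of this stands, and it rules out three stronger readings.

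- A reader might infer that omitting stage biases the result. It does not; step 4 shows this.
- A reader might infer that the trial cannot support a conclusion covering all stages. The article makes no stage-specific claim: its objectives and abstract speak of relatives of lung cancer patients. Randomisation supports the average effect over whoever is enrolled. What the trial cannot show is that the effect is consistent across stages, and covariate adjustment would not change that.
- A reader might infer that allocation is unstratified. The article names no stratification factor, but it is condensed, and such detail may sit in the full protocol.

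The reply fails on one point. The article does state the covariate set for the primary model, and stage is not in it. Stage is a plausible prognostic factor that is already collected, so with unblinded analysts there is good reason to settle its use in advance.

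**Conclusion.** The point holds as a minor improvement. The stated ANCOVA leaves out a collected, plausibly prognostic baseline variable in a population wider than the one in which CALM was tested. The randomised comparison and the average effect over the enrolled mix remain valid.

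The cost is about 0 to 2 points of power for assumed stage effects of 0.2 to 0.5 SD. For a 10-point imbalance the shift in d is 0.01 to 0.05 (assumed effects of 0.1 to 0.5 SD). An imbalance of that size is more likely at 44 per group (24% to 35%) than at 100 per group (8% to 16%). All of these figures rest on assumed stage mixes and stage effects.

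It might seem to follow that the routine-care statement should be limited to stages where the estimate is favourable. The figures do not support that: with 20% to 29% power for an interaction of 0.4, such a rule would rest implementation on an underpowered subgroup result.

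**What to change.** 1. Under Main research question, name UICC stage (advanced versus not, with the cut defined in the plan) as a fixed covariate alongside the baseline score in the primary and secondary ANCOVA, including the interim analysis. Cost: one degree of freedom, with no new data or participants. Date the change, and state whether any outcome data had been examined by then.
2. Pre-specify one arm-by-stage estimate for the primary outcome, with its CI, from a separate model. Label it exploratory because power is low.
3. In the Discussion, word the routine-care conclusion as an average effect over the enrolled stage mix, report that mix, and do not restrict the conclusion by the subgroup result.
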